### Follow-up

Investigators will meet volunteer participants 2, 6, 9, 12, 18, and 24 months after the last rTMS session (Fig. 2). A patient who fails to respond to therapy (no decrease of > 50% in the MADRS score) despite 6 weeks of treatment will continue longitudinal follow-up to avoid selection bias. A telephone call is realized at 15 and 21 months outside the follow-up consultations to keep in contact with the participants and evaluate the EQ-5D, the patient questionnaire including the Word Productivity and Activity Impairment (WPAI) and formal / informal cares consumption, rTMS side effects, and treatment modifications. The study will last 4 years in total (2018–2022) with 24 months dedicated to the enrollment period and 24 months for longitudinal follow-up (Fig. 1).

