## Methods/design

### Study design, setting, and recruitment

This is a health-economic, prospective, randomized, double-blind, multicenter, parallel-arm study funded by the French Ministry of Health (Reference: 030/2018). The sponsor is the Centre Hospitalier Universitaire (University Hospital) of Nantes, France. The patients are randomly assigned to (Fig. 1):
▪ Arm A with active rTMS cure and systematic maintenance M-rTMS for responders (> 50% decrease in MADRS total score);▪ Arm B with a new course of active rTMS at the first sign of depression relapse or recurrence for responders;▪ Arm C with sham cure. In this arm, 50% of responders have systematic placebo rTMS maintenance after the cure (arm C1) and the other 50% have placebo rTMS cure at the first sign of depressive relapse or recurrence (arm C2).

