### Assessments

The following variables are documented during the baseline visit: sociodemographic (date of birth, age, gender, laterality, professional and marital status); medical history (length of illness, duration of the current episode, co-morbidities (psychiatric, addictive, somatic); and current treatment degree of prior therapeutic resistance according to the Maudsley Staging Model (MSM) [37]).

The following variables are regularly evaluated from the beginning to the end of the study, as shown in Table 1: intensity of the depression according to the MADRS [35]; the Beck Depression Inventory 13 items (BDI 13) [38]; the Clinical Global Impression - Severity (CGI-S) [39]; QALY evaluation by the Euroqol Five Dimensions Questionnaire (EQ-5D) [40]; the quality of life with the Short-Form 36 Health Survey (SF-36) [41]; the drug compliance according the Medication Adherence Rating Scale (MARS) [42] and the Compliance Rating Scale (CRS) [43, 44]; and pharmacological and non-pharmacological treatments statement with the eCRF. The response will be defined by a 50% reduction of MADRS, and remission by MADRS score of < 8. All significant side effects or adverse events will be reported in the eCRF by the research team.

**Table 1 Tab1:** Hospital production costs in France for a rTMS session

Medical	
Medical time	€39 (US$43.26)
Nurse time	€32 (US$35.50)
Equipment	€33.57 (US$37.24)
Structural expenses	€23.11 (US$25.64)
Total	€127.68 (US$141.64)

Potential explanatory variables to evaluate the depression economic cost are: formal and informal cares consumption (eCRF questionnaire); depression’s socio-professional aftermath with the Work Productivity and Activity Impairment (WPAI) [45] and eCRF questionnaire; health economic analysis with micro-costing; and data extracted from the National Health System Database of Health (NHSD) with the French hospital expenditure database (E.U. Program of Medicalization of Information Systems [PMSI]). Data from the NHSD include: medical consultations; hospitalizations; pharmacological treatments; work stoppages; daily allowances; care-related transports; imagery and biology; nursing cares; and losses of production in association with the WPAI.

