*C*_*armA*_ and *C*_*armC*_ correspond to the costs of depression in each arm and are the QALYs’ gain associated with the rTMS maintenance versus usual cares without rTMS (placebo). At the end, a univariate and determinate sensibility analysis will be estimate with the Tornado method to evaluate the robustness of the resultants concerning the variation in the cost of rTMS sessions and the hypothesis of their pricing.

To estimate the costs of depression, clinical data matching the eCRF and the NHSD will be applied using the patient identification number. If there is a baseline deviation between arms of the study about the quality of life estimated with the EQ-5D, two analyses will be conducted: one with the quality of life raw score; and another with adjusted scores using a logistic regression model [56]. The cost–utility and EQ-5D analysis will be conducted according to the intent-to-treat (ITT) principle on two samples: one sample with completed cases including participants with completed data; and another with an imputed sample in which missing data about cost and quality of life will be imputed according a multiple imputation method.

The rate of remission with their corresponding 95% CIs at 12 and 24 months will be compared between arm A versus arm C, and arm B versus arm C according to the generalized linear model (logistic model) to consider the repeated measurements as a random factor (stratification factor of the randomization). Plots of relapse-free survival at 12 and 24 months will be estimated according to the Kaplan–Meier method; they will be compared between arms A and B, and between arms B and C using the Log-Rank stratified test in each center. A Cox multivariate analysis will be applied to evaluate the sustainability of the response in the time.

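### Relapse-free survival is analysed in exact time, although listed visits are 2 to 6 months apart and relapse may be noticed differently in the relapse-triggered and fixed-schedule arms

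*Protocol article*

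**What the plan says.** **Visits and calls.** The Follow-up section of the protocol article says: "Investigators will meet volunteer participants 2, 6, 9, 12, 18, and 24 months after the last rTMS session". It adds: "A telephone call is realized at 15 and 21 months outside the follow-up consultations to keep in contact with the participants". The items listed for those calls are EQ-5D, the work-productivity and care-use questionnaire, rTMS side effects and treatment changes. MADRS is not among them. The Assessments section says only that MADRS is rated regularly and points to Table 1, which in the article is a cost table. The study calendar (Fig. 2) is not shown.

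**Treatment after response.** The design section describes "Arm B with a new course of active rTMS at the first sign of depression relapse or recurrence for responders". Arm C2 has the sham equivalent. Arm A has a fixed calendar of 36 maintenance sessions (Interventions), and C1 is its sham counterpart. After month 12, centres choose care freely.

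**Blinding.** Investigators and assessors are told the schedule (systematic or on relapse), but not whether stimulation is active or sham.

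**Analysis.** "Plots of relapse-free survival at 12 and 24 months will be estimated" by Kaplan-Meier. Arms A and B, and arms B and C, are then compared by a log-rank test stratified by centre. Also, "A Cox multivariate analysis will be applied to evaluate the sustainability of the response in the time". The same section says elsewhere that only A v C and B v C will be compared.

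**The concern.** A MADRS-based relapse can be seen only when the MADRS is rated, so on the listed schedule its date is known only to lie between two visits. This matters in two ways.

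1. **Between arms, year 1.** Retreatment in B and C2 depends on someone noticing a relapse, possibly between visits. A and C1 have no such trigger, although their patients attend sessions often. The article describes no ascertainment common to all arms, and assessors know who is on which schedule. A v B sets a fixed-schedule arm against a triggered arm. B v C sets a triggered arm against a control that is half of each. A log-rank difference could then partly reflect how relapse was found.

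2. **Over time.** Visits are further apart in year 2. If relapses are short, fewer are seen, and the curve flattens after month 12 with no change in the true relapse rate.

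**Working it through.** The plan states no figure to reproduce, so the check asks what the listed schedule implies. Times are taken from the end of the first course, as in Statistical analysis.

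**Step 1: gaps.** Visits at 2, 6, 9, 12, 18 and 24 months give gaps of 2, 4, 3 and 3 months in year 1, and 6 and 6 months in year 2.

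**Step 2: mean delay from onset to next visit**, for uniform onset: Σg² / (2Σg).
- Year 1: (4 + 16 + 9 + 9) / 24 = 38/24 = 1.6 months.
- Year 2: (36 + 36) / 24 = 3.0 months.

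**Step 3: share of relapses still present at a visit.** The documents give no relapse durations, so these are assumed.

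Fixed duration D: Σ min(D, g) / Σg. For D = 3, year 1 is (2 + 3 + 3 + 3)/12 = 92% and year 2 is (3 + 3)/12 = 50%.

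| Fixed duration (months) | Year 1 | Year 2 |
|---|---|---|
| 1 | 33% | 17% |
| 2 | 67% | 33% |
| 3 | 92% | 50% |
| 4 | 100% | 67% |
| 6 | 100% | 100% |

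Exponential duration with mean d: Σ d(1 − exp(−g/d)) / Σg.

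| Mean duration (months) | Year 1 | Year 2 | Relative fall |
|---|---|---|---|
| 3 | 62% | 43% | 30% |
| 6 | 78% | 63% | 19% |
| 12 | 88% | 79% | 11% |

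If every relapse lasts until it is seen, the observed yearly risk is the same in both years (50.0% and 50.1% by simulation). The flattening thus depends on short relapses.

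**Step 4: arm contrast at 12 months with equal true hazards.** The plan's 60% response falling to 30% sustained gives 30/60 = 50% relapse among responders, so the hazard is ln 2 / 12 per month. Responders per arm are 64 (60% of 106). Arm A is rated at visits only. Arm B is detected 2 weeks after onset. In both arms a relapse counts only if still present when detected.

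| Assumed relapse duration | Spurious HR, A v B | Log-rank rejection at 5% |
|---|---|---|
| Persistent | 0.93 | 5% |
| Mean 6 months | 0.78 | 17% |
| Mean 3 months | 0.69 | 25% |

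If arm A relapses are instead noticed at its maintenance sessions, the hazard ratio is near 1 or slightly above.

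**Step 5: persistent relapses, smaller sample.** This run uses 51 responders per arm (60% of 85; 85 is about 80% of 106), with triggered patients dated exactly at onset.
- Visit-only detection in both arms: rejection 5.1%.
- B exact, A at visits: 9.0%.
- B exact, C half exact: 5.0%.
- A at visits, C half exact: 6.0%.

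The 12-month cumulative relapse is about 50% in every case. With persistent relapses only the dating shifts, not the count.

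**The case against.** **The visit schedule is the same in every arm, so it creates no arm difference.** This stands: with visit-only detection in both arms the test holds its level (5.1%). A reader might infer that observed relapse rates must differ between arms by design. The documents do not support that. They say when B and C2 are retreated, not that relapse is dated differently for the survival endpoint. A and C1 patients attend frequent sessions and could be noticed as early or earlier.

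**A larger bias can be simulated.** A reader might arrive at an A v B hazard ratio of 0.58 with 48% false positives for 3-month relapses. That result counts arm B relapses even when they have resolved before detection, while arm A relapses must still be present at a visit. With a mean of 3 months, 1 − exp(−0.5/3), about 15%, of episodes end within 2 weeks. Equal counting gives 0.69 and 25%.

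**Short relapses fit the population poorly.** Entry requires an episode of at least 12 weeks that has failed two antidepressant lines. This has weight, and it is why the persistent case is shown. Relapses may still be shortened by retreatment or usual care.

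**Year-2 thinning affects all arms alike.** Correct: by itself it does not bias an arm contrast. Nor does it interact with the triggers, which bind only to month 12.

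**Much may lie elsewhere.** Fig. 2 may list further MADRS ratings, and the definition of relapse is commonly left to the full protocol or SAP; its absence is not the point here. Exact-time methods on visit-assessed events are also common practice. What remains is that the article does state its methods, and they fit the listed schedule badly where detection may differ by arm.

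**Conclusion.** The point holds as an ascertainment mismatch of unknown direction in a secondary endpoint. Relapse known only to within 2 to 6 months is analysed in exact time. A v B and B v C both mix triggered and fixed-schedule follow-up, and assessors know the schedule.

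With relapse durations assumed and arm A seen only at visits, the spurious A v B hazard ratio lies between about 0.93 and 0.7. It is near 1 or slightly above if arm A is noticed at sessions. With persistent relapses the false-positive rate is 5% to 9%, depending on how promptly arm B is dated. No reliable size is offered for B v C with short relapses: the plan states the 60% response only for arms A and B.

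The possible flattening after month 12 is common to all arms and vanishes if relapses last until seen. The primary endpoint, the 12-month ICER, does not use relapse dates. The conclusion rests on the visits and calls listed in the text, as the calendar figure is not shown.

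**What to change.** In Statistical analysis:

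1. Analyse relapse by visit interval, with a grouped-time model (complementary log-log) or an interval-censored model and centre as a factor, in place of exact-time Kaplan-Meier, log-rank and Cox.
2. Use one event rule for every arm and interval: MADRS at the scheduled visits, plus records collected the same way in all arms, such as hospitalisation or ECT from the eCRF and the national health database. Do not let a retreatment course that only B and C2 can receive count as an event by itself.
3. Report A v C1 and B v C2 as supportive, schedule-matched contrasts. C1 and C2 are already randomised separately.
4. State that a flatter slope after month 12 will not be read as sustained response.
5. Reconcile the relapse contrasts (A v B, B v C) with the declared ones (A v C, B v C), and the visit clock (last session) with the analysis clock (end of first course).

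**Cost.** Wording and some programming on data already collected; no new visits. Each matched contrast uses about half of arm C (53 of 106 randomised). With equal responder shares its standard error is √[(1/106 + 1/53) / (1/106 + 1/106)] = √1.5 = 1.22 times that of the full contrast, so it can only be supportive. A relapse that retreatment has reversed before the next visit may be missed under rule 2. The number of retreatment courses in B and C2 should therefore be shown beside the result.

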**Fig. 2 Fig2:**
[figure not shown]
Study calendar

### Assessments

The following variables are documented during the baseline visit: sociodemographic (date of birth, age, gender, laterality, professional and marital status); medical history (length of illness, duration of the current episode, co-morbidities (psychiatric, addictive, somatic); and current treatment degree of prior therapeutic resistance according to the Maudsley Staging Model (MSM) [37]).

The following variables are regularly evaluated from the beginning to the end of the study, as shown in Table 1: intensity of the depression according to the MADRS [35]; the Beck Depression Inventory 13 items (BDI 13) [38]; the Clinical Global Impression - Severity (CGI-S) [39]; QALY evaluation by the Euroqol Five Dimensions Questionnaire (EQ-5D) [40]; the quality of life with the Short-Form 36 Health Survey (SF-36) [41]; the drug compliance according the Medication Adherence Rating Scale (MARS) [42] and the Compliance Rating Scale (CRS) [43, 44]; and pharmacological and non-pharmacological treatments statement with the eCRF. The response will be defined by a 50% reduction of MADRS, and remission by MADRS score of < 8. All significant side effects or adverse events will be reported in the eCRF by the research team.

**Table 1 Tab1:** Hospital production costs in France for a rTMS session

Medical	
Medical time	€39 (US$43.26)
Nurse time	€32 (US$35.50)
Equipment	€33.57 (US$37.24)
Structural expenses	€23.11 (US$25.64)
Total	€127.68 (US$141.64)

Potential explanatory variables to evaluate the depression economic cost are: formal and informal cares consumption (eCRF questionnaire); depression’s socio-professional aftermath with the Work Productivity and Activity Impairment (WPAI) [45] and eCRF questionnaire; health economic analysis with micro-costing; and data extracted from the National Health System Database of Health (NHSD) with the French hospital expenditure database (E.U. Program of Medicalization of Information Systems [PMSI]). Data from the NHSD include: medical consultations; hospitalizations; pharmacological treatments; work stoppages; daily allowances; care-related transports; imagery and biology; nursing cares; and losses of production in association with the WPAI.

### Interventions

Multiple rTMS devices are available in France: Magpro R30 or X100; Magstim Neurostar; Tamas; Powermag; or NBT. All of them feature the Community European (CE) labeling. The most common rTMS devices used are the Magpro R30 or X100 from Magventure (Dantec Company, Copenhagen, Denmark) with an eight-shaped coil and the Magstim Neurostar. The stimulation target is the right dorsolateral prefrontal cortex (Brodmann areas 9 and 46), localized via neuronavigation or by the Beam method. The Beam method, based on the EEG 10/20 target F3, takes into account individual variations and constitutes a valuable approximation of neuronavigation, which is the gold standard [46, 47]. rTMS cures in arms A and B are applied with the following settings: 1 Hz over 8.5 min, 5 days per week (Monday to Friday), 20–30 sessions within 4–6 weeks until remission. The same program is applied in arm C with a sham coil. For systematic rTMS maintenance in arm A, the same parameters are performed with the following rhythm: two sessions per week for 1 month; one session per week for 2 months; and one session every 15 days (36 sessions in total). After the 12-month follow-up, the center is free to choose any therapeutic strategy including M-rTMS or novel rTMS course if needed.

### Primary outcome measures

The primary endpoint in the present study is the ICER analysis (ratio costs / QALY) of these two rTMS therapeutic strategies (arm A or arm B) versus usual chemotherapy, psychotherapy, or ECT without active rTMS (arm C) at 12 months to treat unipolar TRD, according the collective perspective. QALY evaluation is measured by the Euroqol Five Dimension Questionnaire (EQ-5D).

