However, the rates of relapse and recurrence at 6-month follow-up may be comparable to the ECT [27]. These rates are in the range of 60% without consolidation to 30% with consolidation (pharmacological therapies or consolidation ECT) [28]. Having these comments, two therapeutic strategies are possible: a further rTMS cure can be performed at the first sign of relapse or recurrence [29], especially for patients with a good previous response [30]; or systematic maintenance rTMS (M-rTMS) can be carried out in the immediate future [31]. It is, therefore, essential to evaluate the cost-effectiveness of these alternatives treatment for TRD. It is already established that rTMS is more cost-effective (efficiency) than placebo [32] and rTMS is more efficient than a third-line antidepressant treatment in an Australian context [33]. But no controlled study compared in the long term (12 months) the cost-effectiveness of these two rTMS therapeutic strategies versus treatment as usual (TAU) alone (any therapeutic strategy agreed to by patients and psychiatrists including medication, ECT, and psychotherapy). Our main hypothesis is that additional M-rTMS will be more cost-effective at 1 year than TAU alone.

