### Specific aims

The aim of this health-economic study is to investigate the incremental cost-effectiveness ratio (ICER) (ratio costs / quality-adjusted life-years [QALY]) of the curative and maintenance rTMS versus TAU over 12 months in a population of patients suffering from unipolar TRD (Montgomery and Asberg Rating Scale [MADRS] score of ≥ 20). QALY evaluation is measured by the Euroqol Five Dimension Questionnaire (EQ-5D). Moreover, this trial evaluates the budget impact of the most efficient strategy at 5 years, prognosis factors of successful maintenance after rTMS response to a cure, the cost–utility ratio (costs / QALY), and the cost-effectiveness analysis (life years gains [LYG]) (costs/LYG) at 24 months.

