### Statistical analysis

Descriptive analysis of the data collected during each patient evaluation will be carried up until the final evaluation. Specific time points for analysis in the three groups are: baseline; at 1 month after the last rTMS or sham sessions; and 12 and 24 months after the end of the first rTMS or sham course. Continuous variables will be described using median, standard deviation, minimal, maximal, and range for quantitative variables; qualitative variables will be described using frequencies and percentages. No data about quality of life, healthcare consumed, and the cost are available in the literature for this indication, making a priori the calculation of number of individuals needed impossible. The number of participants required for the present study was calculated according to the expected and sustained response in each arm (> 50% decrease in MADRS total score). This rate of responder after the rTMS cure is estimated at 60% in arms A and B at 1 year with 50% of success of rTMS [23, 48]. According to the literature, we hypothesized a rate of 30% maintained response at 1 year for arm A [23, 31, 49, 50] and arm B [23, 50–52], and 11% for arm C [53]. Assuming a 5% (bilateral) type I error, a power of 80%, and an attrition rate of 80%, a total of 318 individuals is required (106 in each arm). The study includes three arms, but only two comparisons will be carried out: arm A versus arm C, and arm B versus arm C.

For the ICER, resources consumed, including costs and QALY, will be presented with average and dispersion for each group. The comparison between cost, QALY, and the years of life gained in each arm, including ICER analysis, will be evaluated with the estimation of their standard deviation and their corresponding 95% confidence intervals (CI) following the non-parametric bootstrap method [54]. Tables will present differences between the three groups including their costs, QALY, and ICER. The ICER is calculated to consider the possibilities of vast dominance between these strategies [55]. For example, the ICER between arms A and C will be calculated as follows:

$$ ICER=\frac{C_{armA}-{C}_{armC}}{QALYs_{armA}-{QALYs}_{armC}} $$

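### The main hypothesis names maintenance rTMS only, the primary endpoint covers arm A or arm B versus C, and the stated 5% level with 95% intervals does not match a sample size that fits 2.5% per comparison

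*Protocol article*

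**What the plan says.** - **Main hypothesis (Background):** "Our main hypothesis is that additional M-rTMS will be more cost-effective at 1 year than TAU alone". Systematic maintenance is the arm A strategy. The same section treats a further cure at relapse, which is arm B, as a separate option.
- **Aim (Specific aims):** the ICER "of the curative and maintenance rTMS versus TAU over 12 months", which is wider than the hypothesis.
- **Primary endpoint (Primary outcome measures):** the 12-month ICER "of these two rTMS therapeutic strategies (arm A or arm B) versus usual chemotherapy, psychotherapy, or ECT without active rTMS (arm C"). The Abstract says the same in substance.
- **Contrasts (Statistical analysis):** "The study includes three arms, but only two comparisons will be carried out: arm A versus arm C, and arm B versus arm C".
- **Error level and size (Statistical analysis, repeated in the Discussion):** "Assuming a 5% (bilateral) type I error, a power of 80%, and an attrition rate of 80%, a total of 318 individuals is required", that is 106 per arm. The basis is sustained response: "we hypothesized a rate of 30% maintained response at 1 year for arm A", the same for arm B, and 11% for arm C.
- **Inference for costs, QALYs and the ICER (Statistical analysis):** standard deviations and "their corresponding 95% confidence intervals (CI) following the non-parametric bootstrap method". No test of the ICER is stated. The Discussion notes that France has no official monetary value for a QALY, and none is fixed for the trial.

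**The concern.** The hypothesis and the primary endpoint do not name the same contrasts. If A v C were favourable and B v C not, both texts would be met. In the reverse case the endpoint section would allow a positive reading, while the hypothesis would not be supported. Limiting the analysis to two comparisons says which contrasts are run. It does not say which of them carries the conclusion.

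The second issue is the level attached to each contrast. The text prints one 5% level and 95% intervals, which reads as 5% for each of two contrasts sharing a control arm. The sample size suggests that a smaller level per comparison was used. If so, the printed intervals are narrower than the design implies. If not, the 5% does not hold for a conclusion that either arm could support. The secondary endpoints also include a budget impact analysis of the most efficient strategy, so the result itself selects what is carried forward. That makes a rule fixed in advance more important.

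**Working it through.** **Inputs.** From Statistical analysis: p1 = 0.30 (arms A and B), p2 = 0.11 (arm C), two-sided 5%, power 80%, 106 per arm. From Randomization: ratio 1:1:0.5:0.5, so A, B and C (C1 plus C2) are equal in size. Assumption: 20% loss. The printed attrition of 80% cannot be literal, because 70/0.2 = 350 per arm.

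**Step 1: reproduce the 106.** Pooled-variance formula, with p̄ = (0.30 + 0.11)/2 = 0.205:

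n = [z(α/2)·√(2p̄(1−p̄)) + z(β)·√(p1(1−p1) + p2(1−p2))]² / (p1−p2)²

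√(2 × 0.205 × 0.795) = 0.5709; √(0.21 + 0.0979) = 0.5549; z(β) = 0.8416; (0.19)² = 0.0361.

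- α = 0.05: (1.960 × 0.5709 + 0.8416 × 0.5549)²/0.0361 = 69.7. Divided by 0.8 this is 87.1, so 88 per arm and 264 in total.
- α = 0.025: (2.241 × 0.5709 + 0.8416 × 0.5549)²/0.0361 = 84.5. Divided by 0.8 this is 105.6, so 106 per arm and 318 in total, as stated. Rounding at each step gives 85, then 107 per arm (321).

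**Step 2: other routes at 5%, same rates, 20% loss.**

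| Method | Evaluable per arm | Enrolled per arm |
|---|---|---|
| Continuity correction | 80 | 100 |
| Fisher's exact test | 78 | 98 |

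Neither gives 106. With 11.6% instead of 11% for arm C (the 12-month response that the Discussion cites for treatment as usual), Fisher's test at 5% gives 84/0.8 = 105, and the continuity-corrected formula gives 85.7/0.8 = 107.1. These come close, but they use a rate other than the one stated for the sizing.

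**Step 3: family-wise error if each contrast is judged at 5%.** With equal arms, a shared control and equal variances (assumed), the two test statistics correlate at 0.5. Under both null hypotheses:

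- P(at least one |Z| > 1.96) = 0.0907. With independence it would be 1 − 0.95² = 0.0975.
- P(at least one Z > 1.96 in favour of rTMS) = 0.0454, against 0.025 for a single contrast.
- At 2.5% per comparison, the two-sided family-wise error is 0.0465.

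**Step 4: power at the stated size.** 106 × 0.8 = 84.8, about 85 evaluable per arm. For 30% versus 11%, power per contrast is 0.873 at 5% and 0.803 at 2.5%. The latter is the planned 80%. This is power for sustained response, not for the ICER.

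**Step 5: cost in precision.** Under a normal approximation, a 97.5% interval is 2.241/1.960 = 1.14 times as wide as a 95% interval.

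**The case against.** The strongest reply is that the design is clearer than the concern suggests. The Abstract, Primary outcome measures and Statistical analysis agree on A v C and B v C. A reader might infer that no contrast decides the trial, or that pooled active rTMS is a third candidate because the aim is worded widely. The documents do not support either: the two contrasts are named, and "only two comparisons will be carried out: arm A versus arm C, and arm B versus arm C" rules out a pooled analysis. What is missing is the rule linking them to a conclusion.

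A reader might also infer a 9% chance of a false primary claim from two tries at 5%. That goes too far for three reasons. The 5% is attached to the sizing on sustained response, while the ICER is to be estimated with bootstrap intervals, without a test or a cost-per-QALY threshold. The 9% counts errors in both directions. And the 106 per arm suggests that alpha had already been split. These objections stand and limit the size of the point.

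Finally, this is a condensed article, and a multiplicity rule may sit in an analysis plan that is not shown. That is fair for the absence of a rule. It does not remove the disagreement between hypothesis and endpoint, or the mismatch between the printed level and the printed sample size, since both are in the article itself.

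**Conclusion.** The point holds in a limited form. The main hypothesis covers arm A only, the primary endpoint covers A or B, and nothing printed says which result, or whether both, must be favourable. The printed 5% and 95% intervals also do not fit the sample size: the stated rates and power give 87 to 88 per arm at 5%, and 106 at 2.5% per comparison.

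The 2.5% is an inference from arithmetic. It rests on 20% loss, the pooled-variance formula without continuity correction, and a control rate of exactly 11%. The error rates of about 9% (either direction) and about 4.5% against 2.5% (in favour of rTMS) apply only if each 95% interval is read as pass or fail, either arm suffices, and both null hypotheses are true. They show what an unstated rule would allow; they are not an established property of this plan. Under either account of the sizing, the rule and the level per comparison need to be written down. This should be corrected, but it does not threaten the design.

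**What to change.** 1. Reword the main hypothesis in the Background, and the Specific aims, to name both strategies, with A v C and B v C at 12 months as the primary contrasts.
2. In Statistical analysis, and in the sample-size paragraph of the Discussion, state that 5% is the overall two-sided level, with 2.5% per comparison (or Holm). The sponsor should check this against its sizing record. Correct the attrition figure in the same sentences.
3. Report 97.5% intervals for the two primary contrasts wherever a confirmatory claim is made. Under Holm this is the level of the first step.

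If the sponsor prefers to keep a hypothesis about maintenance rTMS only, the alternative is to test A v C first at 5% and claim B v C only if A v C succeeds. That gives A v C power of 0.873 on the sizing criterion but makes B v C conditional, which sits less well with the aim of finding the most efficient strategy.

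The choice should be fixed before unblinding. The cost is wording, plus intervals about 14% wider. The sample size stays at 318, with power of about 80% per contrast on sustained response at 85 evaluable per arm.
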